**Independent variables:**

time (To,T1,T2) x group (SDTT, SDTT+)

**Dependent variables:**

*primary clinical outcomes:*

- preferred gait speed (20 m walk test)
- stride length (at preferred speed)
- stride length (at 1.4 km/h)

*secondary clinical outcomes (T1):*

- stride length variability (at preferred speed and at 1.4 km/h)
- stride time (at preferred speed and at 1.4 km/h)
- stride time variability (at preferred speed and at 1.4 km/h)
- step width (at preferred speed and at 1.4 km/h)
- step width variability (at preferred speed and at 1.4 km/h)
- falls
- timed-up-and-go (TUG) test
- 2-minute walk test
- MiniBESTest
- MOCA
- MDS-UPDRS, part III
- mGES

*secondary clinical outcomes (T2):*

- steps per day
- uninterrupted walk durations
- stride time variability
- symmetry

*feedback control variables (T1 all at 1.4 km/h):*

- $R^2$  (feedback model relating foot placement to centre of mass movement)
- RMS error (feedback model relating foot placement to centre of mass movement)
- Position gain (feedback model relating foot placement to centre of mass movement)
- Velocity gain (feedback model relating foot placement to centre of mass movement)

*neural correlates (T1 all at 1.4 km/h):*

- EEG beta power in(pre-)motor areas during walking at preferred speed
- EEG-EMG coherence during walking at preferred speed

**Analysis technique:**

Linear mixed effect models with the interaction of treatment and time in the model and a random intercept for participant (Twisk et al., 2018), controlling for relevant potential confounders (e.g., age, H&Y stage). For the EEG data, we will use cluster-based permutation tests time locked to the gait cycle.

viii. Mechanisms underlying changes in gait performance (3b)

**Population:** 126 PD patients

Associations between clinical outcomes and feedback control

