## 5. The StepuP trial design

### i. Study design

StepuP is a multicenter non-pharmacological randomized controlled trial (RCT) conducted at four clinical centers: Christian-Albrechts-Universität zu Kiel (Kiel), Tel Aviv Sourasky Medical Center (Tel Aviv), University of New South Wales (Sydney), IRCCS Istituto delle Scienze Neurologiche di Bologna (Bologna). 42 PwPD will be enrolled and will be randomized into an intervention group (IG) and a control group (CG) at the clinical sites in Kiel and Sydney. 21 PwPD will be enrolled in Tel Aviv and Bologna and randomized as well into an IG and CG. All Participants will receive a 2-6 week speed-dependent treadmill training (SDTT) aimed at improving gait. Subjects in the IG will receive the same STDD with additional perturbations (SDTT+). Baseline (To) and follow-up (T1 & T2) visits include descriptive, clinical, kinematic and neurophysiological assessment. A 7-day home monitoring with digital sensors will be performed before To and after T2. In Sydney half of the patients in the CG and half of the patients in the IG will have also a second baseline measurement before receiving the SDTT.

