## 6. Statistics and analysis plan

### i. Sample size calculation

The sample size was calculated using the SampSize applicationon for the clinical primary objective (i.e., comfortable gait speed overground, measured in m/sec from a 20 meters walking test), with a significance level (alpha) of 0.05 and power (1-beta) of 0.80, with an allocation ratio of 1:1 in parallel groups. From the available literature, it is known that standard treadmill (SDTT) may improve comfortable overground gait speed up to 0.1 m/sec (from a baseline of 1.26 m/sec) in comparison to standard overground walking and that SDTT with perturbations (SDTT+) may further increase comfortable overground gait speed up to +0.08 m/sec in comparison to SDTT. Thus, we will assume that SDDT+ is superior to SDTT at improving comfortable overground gait speed based on an expected average difference in gait speed between the two groups of +0.08 m/sec with a SD of 0.08 Under this assumption, 17 subjects per group are expected to be enrolled, rising to 20.4 considering a maximum drop-out rate of 20%. This would lead to 41 subjects per trial, rounded to 42 to allow for groups of equal size.

Overall, 126 patients at all clinical sites will in enrolled over a period of 24 months. The recruitment totals for each site is outlined in Table 2. Given the time frame of the trial, recruitment will be monitored on a monthly basis. Should any site encounter recruitment difficulties, other sites have the capacity to recruit additional participants for each cohort as well as to recruit additional cohorts if necessary.

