**Dependent variables:**

*primary clinical outcomes:*

- preferred gait speed (20 m walk test)
- stride length (at preferred speed)
- stride length (at 1.4 km/h)

*secondary clinical outcomes (T1):*

- stride length variability (at preferred speed and at 1.4 km/h)
- stride time (at preferred speed and at 1.4 km/h)
- stride time variability (at preferred speed and at 1.4 km/h)
- step width (at preferred speed and at 1.4 km/h)
- step width variability (at preferred speed and at 1.4 km/h)
- falls (diary)
- timed-up-and-go (TUG) test
- 2-minute walk test
- MiniBESTest
- MOCA
- MDS-UPDRS, part III
- mGES

*secondary clinical outcomes (T2):*

- steps per day
- uninterrupted walk durations
- stride time variability
- symmetry

*feedback control variables (T1 all at 1.4 km/h):*

- $R^2$  (feedback model relating foot placement to centre of mass movement)
- RMS error (feedback model relating foot placement to centre of mass movement)
- Position gain (feedback model relating foot placement to centre of mass movement)
- Velocity gain (feedback model relating foot placement to centre of mass movement)

*neural correlates (T1 all at 1.4 km/h):*

- EEG beta power in(pre-)motor areas during walking at preferred speed
- EEG-EMG coherence during walking at preferred speed

Linear mixed effect models with the interaction of treatment and time in the model and a random intercept for participant nested within center (Twisk et al., 2018), controlling for relevant potential confounders (e.g., age, H&Y stage). For the EEG data, we will use cluster-based permutation tests time locked to the gait cycle.TT)

vii. Independent RCTs SDTT vs SDTT+ (3a)

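### Analysis 3a does not say that Bologna and Tel Aviv form one SDTT+VR trial of 42, and its model has no centre-by-time term for that two-centre trial

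*Protocol*

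**What the plan says.** - **Size per trial (Protocol 6.i).** The calculation is made "with a significance level (alpha) of 0.05 and power (1-beta) of 0.80" and "with an allocation ratio of 1:1 in parallel groups", for an "expected average difference in gait speed between the two groups of +0.08 m/sec with a SD of 0.08". It gives 17 per group, 20.4 after the drop-out allowance, and then: "This would lead to 41 subjects per trial, rounded to 42 to allow for groups of equal size". The overall total is 126.
- **Enrolment (Protocol 5.i and Table 2).** Kiel and Sydney each have 21 + 21. For the other two sites, "21 PwPD will be enrolled in Tel Aviv and Bologna and randomized as well into an IG and CG". Table 2 gives SDTT+VR against SDTT as 11 and 10 in Bologna, and 10 and 11 in Tel Aviv.
- **Analysis 3a (Protocol 6.vii).** The heading speaks of independent RCTs, but no population is given and the trials are not listed. The model is "Linear mixed effect models with the interaction of treatment and time in the model and a random intercept for participant", with adjustment for potential confounders such as age and H&Y stage. Centre is not mentioned.
- **Analysis 2a (Protocol 6.vi).** The otherwise similar model has a "random intercept for participant nested within center".

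**The concern.** The total of 126 equals 3 x 42, so the sample size assumes three trials. Two sit in one centre each. The third, SDTT+VR, exists at the planned size only if Bologna and Tel Aviv are joined, and the protocol never says so. The model written for 3a suits the two single-centre trials. It makes no provision for a trial whose patients are allocated within two centres.

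Two things follow. First, the choice between one analysis of 42 and two of 21 is left open and could be made after the data are seen. Second, in a pooled analysis the model has no term for a difference between the centres in mean change from T0 to T1. Such a difference is conceivable: training lasts 2 to 6 weeks (5.i), and the gap between sessions may depend on each centre's logistics (5.iv). It would inflate the residual variance of the treatment-by-time test. Because the allocation is 11:10 and 10:11, a small part would also pass into the estimated effect.

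**Working it through.** **Inputs from Protocol 6.i and Table 2.** Difference 0.08 m/s, SD 0.08 m/s (standardised effect 1.0), alpha 0.05, power 0.80, 1:1 allocation. The protocol does not state sidedness; two-sided is used because it reproduces the stated n. It also does not say whether the SD is of gait speed or of change. Below it is taken as the within-centre SD of the T0-T1 change, which is an assumption.

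**1. The plan's own figure.** A two-sided two-sample t-test with effect 1.0 needs 16.71, so 17 per group, as stated. Then 17 x 1.2 = 20.4 per group, 40.8 in total, rounded to 41 and then to 42. Power at 17 per arm is 0.807, and at 21 per arm 0.885.

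**2. What makes up 42.** Bologna plus Tel Aviv gives 11 + 10 = 21 on SDTT+VR and 10 + 11 = 21 on SDTT. Then 42 (Kiel) + 42 (Sydney) + 42 (the two VR sites) = 126.

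**3. Pooled, with the model as written, and no centre difference in change.** A difference in baseline speed cancels from the treatment-by-time contrast. In a mixed-model simulation (400 runs, so an error of about 2 points, at 17 per arm), power was the same with and without a centre main effect: 83.5% for both with no baseline difference, and 80.0% for both with a baseline difference of 0.2 m/s. A centre main effect, or an intercept nested in centre as in 2a, therefore does not help.

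**4. Pooled, with the model as written, and a centre difference D in mean change.** With centres of equal size, the SD of change becomes sqrt(0.08² + D²/4). The values of D are assumed; the documents give none.

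| D (m/s) | SD of change | Power, 17 per arm | Power, 21 per arm |
|---|---|---|---|
| 0 | 0.0800 | 0.81 | 0.89 |
| 0.04 | 0.0825 | 0.78 | 0.87 |
| 0.06 | 0.0854 | 0.75 | 0.84 |
| 0.08 | 0.0894 | 0.72 | 0.81 |

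**5. Bias from the mirrored split.** D x (11/21 - 10/21) = 0.048 D. At D = 0.08 this is 0.004 m/s, about 5% of the target difference.

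**6. Direction.** The formula in step 4 leaves this bias out. In simulated change scores with 9:8 and 8:9 evaluable, power without a centre term on change was 0.76 or 0.81 at D = 0.04, and about 0.67 or 0.79 at D = 0.08, depending on which centre improves more. The step 4 values lie inside these ranges. With a centre term on change, which is what centre-by-time provides, power was about 0.80 to 0.81 throughout and the mean estimate stayed at 0.080.

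**7. Each VR centre alone.** 11 against 10 gives 0.584. After 20% loss, 9 against 8 gives 0.486 and 8 against 8 gives 0.461.

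**The case against.** The strongest reply is that the design already shows the intent. The mirrored 11:10 and 10:11 split gives 21:21 only when the sites are joined, 126 is 3 x 42, and the home-assessment section counts SDTT+VR as one arm across both sites. This stands. A reader might infer that 3a is a single-centre model and that the VR comparison therefore runs at 46% to 58% power. The documents do not support that: 6.vii does not say the analysis is run by centre, and the sample size points the other way.

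A reader might also infer that omitting centre by itself forfeits the 80%. It does not: step 3 shows power at about its planned level when the centres differ only in baseline speed. A loss needs a difference in mean change, and the values that matter are large beside the plan's own figures, since 0.08 m/s is the whole assumed benefit of SDTT+. At full enrolment D would have to reach about 0.08 to bring power down to 80%. If the SD of 0.08 already contains variation between centres, the tabulated loss is partly counted twice. The bias is too small to matter on its own.

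It can further be said that a centre-by-time term is detail for a statistical analysis plan, and that the text around 6.vi is visibly broken by extraction, so a population line may have been lost. Both lower the weight of the point. But the protocol does write out a model for 3a, and a better one for the two-centre trial costs almost nothing.

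**Conclusion.** The point holds as a minor one. Section 6.vii does not state that Bologna and Tel Aviv form one SDTT+VR trial, although the sample size requires it, and the model it gives has no term for a difference in change between those centres. Pooled as intended, the stated 80% power holds if the centres change by similar amounts. The possible erosion, to about 0.78 or 0.72 at 17 per arm for assumed differences of 0.04 or 0.08 m/s, rests on two assumptions: that SD 0.08 is the within-centre SD of change, and that a difference of that size exists. The documents establish neither. This is a nearly free improvement to the stated model; no loss of the stated power has been demonstrated.

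**What to change.** In section 6.vii, name the three trials and state that Bologna and Tel Aviv are analysed together as one SDTT+VR trial of 42. For that trial, add fixed centre and centre-by-time terms alongside treatment-by-time; a centre main effect alone, or the nested intercept of 2a, is not enough. Keep the participant-intercept model for the single-centre Kiel and Sydney trials. Label any separate Bologna or Tel Aviv result as descriptive, noting about 58% power at full enrolment under the plan's own inputs.

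The cost is a sentence or two of text and about two degrees of freedom (two parameters for T0 and T1, three if T2 is kept as a separate time level), which is negligible with 34 to 42 patients. No new patients or data are needed.

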## vii. Pre-Training (To)

Prior to the *training phase*, participants in all groups across all centers will undergo a standardized *functional assessment*, including measurement of clinical outcomes and a gait analysis during which EEG, EMG and kinematics data will be collected. A video of the participants head will be taken to determine the electrode position. In particular, a computer vision algorithms will detect the position of each electrode in 3D in relation to anatomical landmarks. This will allow a standardized 2D cartesian projection that could be shared across centers for statistical analysis. Please note that no video files will be shared, only 2D coordinates will be, which do not contain any personalized information.

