## **F. Kinematics and Neurophysiological measures**

- F1. Kinematics: 3D motion capture data will be recorded at T0, T1 and T2.
- F2. Electroencephalography (EEG): EEG records an electrical signal from the surface of the scalp and can be used to describe brain activity. This will be recorded at T0, T1 and T2.
- F3. Electromyography (EMG): Surface EMG records the electrical activity of superficial muscles through electrodes placed on the skin, and it is commonly used in clinical and research settings to assess muscle function, fatigue, and activation patterns. This will be recorded at T0, T1 and T2.

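### The EEG comparison between arms in 2a and 3a moves to a permutation test with no stated place for the T0 recording or the covariates, nor for centre in pooled 2a; adding T0 and centre is a free gain in power

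*Protocol*

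**What the plan says.** Protocol 6.vi (2a) and 6.vii (3a) plan linear mixed models with a treatment-by-time interaction, adjusted for confounders such as age and H&Y stage. In 2a the random intercept is for participant nested within centre; in 3a it is for participant only. Both sections then give EEG one sentence: "For the EEG data, we will use cluster-based permutation tests time locked to the gait cycle". Neither names the contrast, the role of T0, the covariates or the units within which labels are permuted.

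Both sections list the EEG outcomes under "neural correlates (T1 all at 1.4 km/h"). Section 6.vii also gives its independent variables as time (T0, T1, T2) by group, without exempting EEG.

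EEG is recorded at T0, T1 and T2 (5.xii.F). T0 data are collected before assignment (5.xiv). Electrode positions are put on a common footing for pooling: "This will allow a standardized 2D cartesian projection that could be shared across centers for statistical analysis" (5.vii). Participants are randomised at each clinical site (5.i), with near-equal arms in each centre (Table 2). The mechanism analysis (6.viii, 3b) uses EEG change from T0 and multilevel models for site.

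**The concern.** Walking EEG can be expected to differ between patients, and possibly between laboratories, for reasons unrelated to training. The T0 recording measures much of that difference before randomisation. An arm comparison that leaves it out counts it as error, and so does a pooled comparison that ignores centre. The mixed model has a place for T0 through its time factor and, in 2a, for centre. The EEG sentence provides for neither.

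The same kind of test is used for the patient-control comparison (6.v, 1b), which has no baseline to use. Elsewhere, where change is meant, the protocol writes it out, as in 3b. A T1-only EEG comparison is therefore one natural reading of 2a.

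The protocol's rationale (4.i) names cortical activity as the neural correlate of training, and neurophysiological measures are secondary endpoints (4.iii). A null EEG contrast from an inefficient test would be hard to interpret. An undefined contrast can also be chosen after the data are seen.

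**Working it through.** **The plan's own calculation.** Section 6.i powers gait speed only, "with a significance level (alpha) of 0.05 and power (1-beta) of 0.80" and an "expected average difference in gait speed between the two groups of +0.08 m/sec with a SD of 0.08". Sidedness is not stated; two-sided is assumed. The normal formula gives n = 2 × (1.960 + 0.842)² × (0.08/0.08)² = 15.7, so 16 per group. The t distribution gives 17 (power 0.807), and 17 × 1.2 = 20.4. The stated figures reproduce. They carry no EEG effect size, SD, T0-T1 correlation or centre variance, so these are assumed below.

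**Inputs for the EEG contrast.**
- Patients: Table 2 sums to 63 per arm; 63 × 0.8 = 50.4, so 50 per arm after the planned maximum drop-out of 20%.
- Effect: 0.5 SD (assumed).
- T0-T1 correlation ρ: 0.3 to 0.7 (assumed).
- Two-sided 5%, with one scalar per patient standing in for the cluster statistic.

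**Formula.** Power = Φ(0.5 × √(50/2) / f − 1.96) = Φ(2.5/f − 1.96), where f is the SD factor:
- T1 only: f = 1
- change T1 − T0: f = √(2(1 − ρ))
- T1 adjusted for T0: f = √(1 − ρ²)

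Worked at ρ = 0.5: T1 only, Φ(0.54) = 70.5%. Change, f = 1, also 70.5%. Adjusted, f = 0.866, Φ(0.927) = 82.3%.

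| ρ | T1 only | Change | T0-adjusted | Gain over T1 only | Gain over change |
|---|---|---|---|---|---|
| 0.3 | 70.5% | 56.1% | 74.6% | 4 points | 18 points |
| 0.5 | 70.5% | 70.5% | 82.3% | 12 points | 12 points |
| 0.7 | 70.5% | 89.8% | 93.8% | 23 points | 4 points |

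**Centre, pooled 2a.** Suppose a centre-adjusted test has 80% power and a share c of the variance lies between centres. A T1 test ignoring centre then has Φ(2.802 × √(1 − c) − 1.96): 78% at c = 0.05, 76% at 0.10, 71% at 0.20 and 65% at 0.30. In a change score a stable additive centre difference cancels, so this penalty belongs mainly to the T1-only reading.

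**Simulation of both together.** Settings: 100 completers split 34/34/16/16 by centre, effect 0.5 within-centre SD, 800 replicates, 299 permutations. T1-only with labels exchanged freely was compared with T0- and centre-adjusted residuals permuted within centre:

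| ρ | Centre share | T1 only, free | Adjusted, within centre |
|---|---|---|---|
| 0.3 | 0% | 70% | 72% |
| 0.5 | 0% | 70% | 82% |
| 0.5 | 20% | 64% | 80% |
| 0.5 | 40% | 53% | 81% |
| 0.7 | 20% | 63% | 92% |

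The simulated gain at ρ = 0.3 is 2 points against 4 from the formula, hence the range of 2 to 4. At a 40% centre share, free permutation of T1 values had a type I error of about 2% instead of 5%, so it was conservative.

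**The case against.** A reader might infer that the plan throws the T0 EEG away, permutes labels freely across centres and so loses substantial power. The documents do not support that.

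- Section 6.vii puts T0 in the time-by-group design of 3a, so a T1-T0 contrast is allowed there.
- The T1 tag on the EEG outcomes also sits on the secondary clinical and feedback-control outcomes, which stay in the treatment-by-time model. It cannot show a T1-only analysis.
- The 3a mixed model has no centre term, so EEG loses none there.
- Free exchange of labels is stated nowhere. A cluster-based test can be run on change scores or residuals and within strata.

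These points stand. So does the defence of the test itself, which deals with multiplicity over the gait cycle. The main neural hypothesis is examined in 3b, where change from T0 and site are used. The contrast and the permutation scheme may be set out in a SAP that was not available for this review.

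What remains is narrower. The EEG sentence as written provides for neither T0 nor covariates, nor for centre in pooled 2a. Under both readings of the contrast, T1-only or change score, the T0-adjusted test had the higher power in every setting computed.

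**Conclusion.** The point holds as a free efficiency improvement to secondary endpoints. It is not a demonstrated error, and no fixed power loss can be attributed to the plan.

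If the test were T1-only, adjustment would be worth little at a correlation of 0.3 without centre differences and a good deal from about 0.5 upwards. If it were run on change scores, the gain would shrink as the correlation rises. All of this rests on the assumed correlation, centre share and 0.5 SD effect, and on a scalar approximation to the cluster statistic.

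The centre part concerns 2a. It extends to 3a only if Bologna and Tel Aviv are analysed as one trial, which Table 2 and the 42 patients per trial in 6.i suggest but 6.vii does not state.

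**What to change.** Keep the cluster-based permutation test in 2a and 3a and define its arm statistic. At each channel and gait-phase point, regress T1 (and separately T2) on the patient's own T0 value, plus centre wherever centres are pooled: 2a, and Bologna with Tel Aviv if they form one trial. Take the arm statistic from that regression or its residuals, and permute arm labels only within centre. In Kiel and Sydney analysed alone, only the T0 adjustment applies. Say also whether age and H&Y stage enter the same regression, as they do in the mixed models.

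The cost is about two sentences of analysis text and a few lines of code, fixed before the arms are compared. No new data are needed. The one downside is that a patient without a usable T0 EEG needs the covariate imputed (for example by its mean) or is lost from this contrast; the text should say which.

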**Dependent variables:**

*primary clinical outcomes (T1-To / T2-To):*

- $\Delta$  preferred gait speed (20 m walk test)
- $\Delta$  stride length (at preferred speed and at 1.4 km/h)

*secondary clinical outcomes (T1-To / T2-To):*

- $\Delta$  stride length variability (at preferred speed and at 1.4 km/h)

- $\Delta$  stride time (at preferred speed and at 1.4 km/h)
- $\Delta$  stride time variability (at preferred speed and at 1.4 km/h)
- $\Delta$  step width (at preferred speed and at 1.4 km/h)
- $\Delta$  step width variability (at preferred speed and at 1.4 km/h)

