|                      | Local divergence exponent
Foot placement model (multiple linear regression) : 
 
- Relative explained variance (<math>R^2</math>)
 
- Standard deviation of residual (i.e. foot placement error)
 
- Regression coefficients
 
                                                                                                                                                                                     | Kinematics                             |
|                      | Beta-band Power in motor areas
Cortico-muscular coherence                                                                                                                                                                                                                                                                                                                                                                                                                     | Neurophysiological                     |
|                      | Steps per day
Amount and length of uninterrupted walk durations
Stride time variability
Symmetry                                                                                                                                                                                                                                                                                                                                                                        | Home assessment                        |
|                      | Adverse events
Falls and injuries
Mobility
Fatigue
Exercise Adherence
Health services use                                                                                                                                                                                                                                                                                                                                                                         | Weekly Calendars and Safety Monitoring |

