#### *Kinematic and neurophysiological measures*

We will assess preferred gait speed using a 20-m walk test (Primary outcome).

Participants start walking on the treadmill for 7 minutes for familiarization. After that, they will then walk at a fixed speed of 1.4 km/h for 5 minutes, to assess the secondary outcomes, step-width and stride-time and the variance of these parameters, from data of at least 100 strides. The fixed 1.4 km/h is attainable for an estimated 95% of patients with moderate PD. However, for those who cannot attain 1.4 km/h at To, their preferred walking speed To will be their fixed speed during all functional assessments. The treadmill assessment will be repeated at their preferred speed. Additionally, during Treadmill walking data from the EEG and EMG will be collected to derive beta-band power in motor areas and calculate cortico-muscular coherence (CMC) between brain and muscle activity.

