### **Independent variables:**

*feedback control variables (T1-To / T2-To, at 1.4 km/h):*

- $\Delta R^2$  (feedback model relating foot placement to centre of mass movement)
- $\Delta$  RMS error (feedback model relating foot placement to centre of mass movement)
- $\Delta$  Position gain (feedback model relating foot placement to centre of mass movement)
- $\Delta$  Velocity gain (feedback model relating foot placement to centre of mass movement)

*neural correlates (T1-To / T2-To, at 1.4 km/h):*

- $\Delta$  beta power during walking at preferred speed
- $\Delta$  EEG-EMG coherence during walking at preferred speed

Associations between feedback control variables and neurological correlates

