### **Analysis technique:**

We will correlate changes in primary outcomes (e.g., walking speed) with changes in behavioural (foot placement coordination) and neural (EEG beta band power, cortico-muscular coherence) outcomes. Multilevel models will be used, to account for data collected at different sites. For outcomes T2-To, potential predictors of clinical outcomes will include independent variables with a time lag (T1-To) and without time lag (T2-To).

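### Analysis 3b correlates change in step-width variability at 1.4 km/h with foot-placement regression measures that probably come from the same strides, so zero correlation is probably the wrong null for these pairs

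*Protocol*

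**What the plan says.** Protocol 6.viii (analysis 3b) sets out associations of change scores in 126 patients. Among the secondary dependent variables is change in "step width variability (at preferred speed and at 1.4 km/h". The independent variables are headed "feedback control variables (T1-To / T2-To, at 1.4 km/h" and include R², two gains and "RMS error (feedback model relating foot placement to centre of mass movement". The analysis technique is to correlate changes in outcomes "with changes in behavioural (foot placement coordination) and neural (EEG beta band power, cortico-muscular coherence) outcomes", with multilevel models for site.

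The Trial Summary describes a "Foot placement model (multiple linear regression" and lists three outputs from it: R², the regression coefficients, and "Standard deviation of residual (i.e. foot placement error". All three therefore come from one fit.

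For the T0 treadmill walk, Section 5.vii.A gives this condition: "fixed speed of 1.4 km/h for 5 minutes, to assess the secondary outcomes, step-width and stride-time and the variance of these parameters". A minimum of 100 strides applies. The section describes no second walk at 1.4 km/h. Sections 5.ix.A and 5.xi.A instead place the five-minute walk at T1 and T2 at preferred speed, while keeping the text about the fixed 1.4 km/h.

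The protocol does not state the axis of foot placement, its reference point, or which strides feed the regression.

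**The concern.** In any least-squares fit the residual variance equals (1 − R²) times the variance of the fitted quantity. If that quantity is step width, RMS error is a component of the outcome, R² has the outcome's variance as its denominator, and the gains generate the rest of that variance. Chance fluctuation in one bout then moves both sides of the correlation together, and a change score carries that fluctuation from both visits.

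Work Package 2 hypothesises that gait improves because foot placement is better coordinated with centre-of-mass (CoM) movement. For RMS error the shared noise gives a positive correlation (less error, less variability), which is the sign expected under that hypothesis. It could be reported as mechanism when no patient has changed. For R² the shared noise is also positive (higher R², more variability), which runs against the hypothesis and could be misread as contrary evidence. Section 6.ii calls mechanism the main aim, so the reading of these pairs matters even though they are secondary.

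**Working it through.** **Inputs from the protocol.** N = 126 (Table 2: 21 + 42 + 42 + 21 = 126); with 20% loss, 126 × 0.8 ≈ 100. At least 100 strides per walk. Alpha 0.05, taken from the sample-size section and treated as two-sided. The protocol gives no expected correlation for 3b, so there is no planned figure to reproduce.

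**Assumptions.** Foot placement is mediolateral relative to the stance foot, so its variance is the step-width variance. Both sides use the same strides. Model R² is between 0.3 and 0.85, as the protocol gives no value. There are two predictors, and no patient truly changes.

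**Large-sample correlations under no change.** Write V for step-width variance, scaled to 1, and n for strides.
- RMS error: the sampling variance of V is 2/n. The residual variance has sampling variance 2(1 − R²)²/n, and its covariance with V is the same. Hence r = 1 − R².
- R²: r = +√(R²/2).
- Gains, taking two uncorrelated predictors of equal weight: r = √(R²(1 − R²)).

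| Model R² | RMS error, 1 − R² | R², √(R²/2) | Each gain, √(R²(1 − R²)) |
|---|---|---|---|
| 0.3 | 0.70 | 0.39 | 0.46 |
| 0.5 | 0.50 | 0.50 | 0.50 |
| 0.7 | 0.30 | 0.59 | 0.46 |
| 0.85 | 0.15 | 0.65 | 0.36 |

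With 124 degrees of freedom, significance at 0.05 needs |r| above 0.175. Every entry except RMS error at R² = 0.85 exceeds that.

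**Simulation.** N = 126, 100 strides per visit, two visits with identical true parameters, 400 trials per setting, Pearson correlation of change scores:

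| Model R² | ΔRMS error: r | p < 0.05 |
|---|---|---|
| 0.3 | 0.69 | 100% |
| 0.5 | 0.50 | 100% |
| 0.7 | 0.30 | 92% |
| 0.85 | 0.15 | 37% |

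- ΔR²: r about +0.4 to +0.6, significant in 98–100%.
- Δ gains: r about 0.3 to 0.6, significant in 88–100%; lower (44–70% in one setting) for a gain that carries the smaller share of the explained variance.
- With N = 100 or 200 strides, and with R² and step-width SD varying between patients, r is nearly unchanged; rejection is 39–100% for RMS error and 95–100% for R².

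**If the assumption holds only in part.** At R² = 0.5, when the modelled placement makes up 75%, 50% or 25% of step-width variance, the RMS pair gives r = 0.37, 0.25 or 0.12 and is significant in 99%, 82% or 28%.

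**Disjoint strides.** With feedback measures from odd strides and variability from even strides, rejection is about 3–8% for identical patients. With separate strides and unequal variances between patients it is 7–10%. If CoM amplitude also varies by 10% between sessions with coordination unchanged, the split holds RMS error at about 3–5% and the gains at 3–6%, but ΔR² is still significant in 16–97%, because amplitude moves both R² and step-width variance.

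**The case against.** The premises are not in the protocol. It gives no axis, no reference point and no stride selection for the foot-placement model, and the stride minimum refers to step width and stride time. The T1 and T2 text leaves unclear which bout feeds which variable. Stride selection may be left to a SAP, which is not at hand. Section 6.viii names walking speed as its example outcome and states no null or alpha for 3b. The simulations take the extreme case in which all change is estimation noise.

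Much of this stands, and it makes the point conditional. It does not remove it. The protocol itself puts these variables on opposite sides of one association at one speed, describes a single 1.4 km/h walk and states no safeguard.

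A reader might infer that the pairs correlate by construction, that the test almost always rejects, and that 3b would therefore show a mechanism in unchanged patients. The documents do not support that. Shared strides and a mediolateral axis are inferences. Rejection for RMS error falls to 37% at R² = 0.85, and to 28% when modelled placement is a quarter of step-width variance. Only the RMS artefact has the hypothesised sign. Nor does replacing R² with the gains cure the problem, since the gains are coupled too on shared strides.

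**Conclusion.** The point holds conditionally. If foot placement is mediolateral from the stance foot and the same bout supplies both sides, zero is the wrong null for change in step-width variability at 1.4 km/h against R², RMS error and gains. The artefact is large for R² at every value tried, large for RMS error when model R² is 0.7 or below, and modest for RMS error at 0.85. If placement is modelled fore-aft, the same issue reaches stride-length variability, less exactly.

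The scope is narrow: variability outcomes at the same speed as the feedback measures. Overground gait speed, from the 20-m walk test, is not coupled in this way, nor are preferred-speed outcomes from a separate bout. It would be wrong to conclude that analysis 3b as a whole is invalid. The change is worth making because it is cheap and these pairs bear on the stated main aim.

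**What to change.** In 6.viii:

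1. State the axis and reference point of foot placement.
2. Compute all feedback measures (R², RMS error, gains) and the 1.4 km/h variability outcomes from disjoint strides, for example odd and even, then swap the halves and average.
3. Even with the split, do not test ΔR² against a variability outcome. Use the gains for those outcomes, and only with the split.
4. Report same-bout RMS error against step-width variability as a descriptive split of variance into residual and CoM-explained parts, not as evidence of mechanism.
5. Reconcile 5.ix.A and 5.xi.A, which put the T1 and T2 five-minute walk at preferred speed, with the 1.4 km/h data that 6.viii needs at those visits.

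The cost is protocol wording and a few lines of processing code. Halving the strides raises the sampling error of each patient's estimates by up to about √2, partly recovered by swapping and averaging. The gait-speed associations stay as they are.
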